#### Definitions

##### Adverse event

An AE is any untoward clinical event in a trial participant, which may or may not be related to the study intervention. The clinical event could be an unfavourable and unintended symptom, sign, medical condition, abnormality or disability that has appeared or worsened during the course of the trial, regardless of a causal relationship to the study intervention.

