The evidence for the effectiveness of interventions to provide children a smoke-free environment at home is scarce. A recent Cochrane review concluded that, despite several studies on parental education and counselling programmes, their effectiveness in reducing children’s tobacco smoke exposure has not been clearly demonstrated.^15^ An alternative approach, for which there is also only very limited research, is to encourage children themselves to negotiate smoking restrictions in their households.^16^ We developed a school-based SFI and found through a feasibility trial in Dhaka, Bangladesh (24 schools, 781 children) that it was acceptable and successful in getting children to negotiate implementation of smoking restrictions at home (OR 3.9; 95% CI 2.0 to 7.5).^17^ Schools were also willing to participate and be randomised in a trial. Encouraged by these findings, we now wish to assess if the success of this intervention also translates to reduce SHS exposure in children and improves their health outcomes and academic achievements.

The principal question for our planned follow-on definitive trial is: What is the effectiveness and cost-effectiveness of a school-based SFI in reducing children's exposure to SHS (primary outcome), the frequency and severity of respiratory illnesses, healthcare contacts, school absenteeism, smoking uptake and in improving their lung function, quality of life and school performance?

Prior to conducting a definitive trial to answer the above question, we wish to first conduct a pilot trial that informs the parameters required for conducting the definitive trial.^18^ Our *specific research questions* for this pilot study are therefore to ascertain:
What are the recruitment and attrition rates for schools (clusters) and children?What is the feasibility and acceptability of measuring the primary and secondary outcomes?What is the likely effect size and its variance in relation to the primary outcome measure?What is the intracluster correlation coefficient (ICC) among children for the trial outcomes?What is the fidelity of delivering SFI in schools?What are the costs associated with delivering SFI through schools?What would facilitate and hinder in scaling up SFI in schools and their curriculum?What is the frequency and nature of any adverse events (AE)?

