#### Frequency and severity of respiratory symptoms

Participating children will keep diaries and record respiratory symptoms on a nominal severity scale from 0 to 3 as used by Chauhan *et al*.^20^ For each item, ‘0’ representing the absence of a symptom, 1 representing mild, 2 representing moderate and 3 representing the greatest severity level. The upper respiratory tract symptoms will include having a runny nose or sneezing, blocked or stuffy nose, sore throat or hoarse voice, headaches or face aches, aches or pains elsewhere, and feeling chill, fever or shivers. The lower respiratory symptoms will include cough on waking, wheeze on waking, cough during the day, wheeze during the day, shortness of breath during the day, night cough and wheeze or shortness of breath during the night. Scores will be recorded daily and added up to give daily upper and lower respiratory-tract scores, respectively.

Three hundred and sixty diaries to record respiratory symptoms will be printed and given to all participating children. These diaries will have three sections. Section 1 will record symptoms from the day intervention is delivered until the end of month 2; section 2 from the start of month 3 until the end of month 6; and section 3 from the start of month 7 until the end of month 12. At each follow-up, one section will be taken out of the diary by the researchers and data will be entered in the database. All children will provide data on section 1. Only those children whose cotinine levels are indicative of passive smoking at baseline will provide data on sections 2 and 3. Children will be told whether to stop or keep collecting information in their diaries in a letter.

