### AEs procedures

We are expecting a minimal number of adverse and no serious AEs (SAEs) during the study. SFI is an educational intervention and has been very well received in our previous studies^17^ without leading to any directly related AEs. Nevertheless, there will be a vigilant surveillance system in place for AEs occurring during the course of the trial with particular emphasis on identifying, recording, reporting and managing any SAEs. We will sensitise schoolteachers to look for signs of any AEs resulting from the interactions between children and their parents. We will also encourage children and parents to report any related adversities.

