#### Detecting, recording and reporting of AEs and SAEs

In the event of any AE reported by the child, their parents/carers or schoolteachers, the research assistant will complete an AE form, which will include medical diagnosis, if relevant and available. The research assistant will also call the trial manager on the same day providing a verbal report of the event. The trial manager will ensure that the event is classified appropriately after receiving the verbal report. All AEs will be reported to the principal investigator, Bangladesh (RH) within 3 days of detection. AE data will be collated and reported to the trial sponsors and National Bioethics Committee at six monthly intervals. These must also be reported to the Study Operational Committee (SOC) and the Independent Trial Steering Committee (ITSC) at their regular meeting. All AEs that have the potential to develop into SAEs will be followed to resolution or stabilisation and reported as SAEs if they become serious. All SAEs must be reported to the principal investigator within 24 h of detection and should also be reported to the trial sponsors and National Bioethics Committee within three working days. All serious events must also be reported to all study investigators and the chair of the ITSC within 3 days. The chief investigator will have the overall responsibility to ensure that all AEs are reported according to the above protocol.

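### The adverse event definition covers clinical events only, so non-clinical family harm, the harm most specific to this intervention, would not be counted

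*Protocol article*

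**What the plan says.** All references are to the protocol article.

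- **Introduction, specific research questions.** The last of the eight pilot questions is "What is the frequency and nature of any adverse events (AE").
- **AEs procedures.** The expectation is low: "We are expecting a minimal number of adverse and no serious AEs (SAEs) during the study". Surveillance is then pointed at one route: "We will sensitise schoolteachers to look for signs of any AEs resulting from the interactions between children and their parents". Children and parents are also encouraged to report adversities connected with the study, a term that is not defined.
- **Definitions, Adverse event.** "An AE is any untoward clinical event in a trial participant, which may or may not be related to the study intervention". An illustration, which is limited to the trial period and applies irrespective of cause, begins: "The clinical event could be an unfavourable and unintended symptom, sign, medical condition, abnormality or disability that has appeared or worsened during the course of". Serious AEs are likewise defined by clinical occurrences.
- **Detecting, recording and reporting.** "In the event of any AE reported by the child, their parents/carers or schoolteachers, the research assistant will complete an AE form". The form takes a medical diagnosis only where there is one to give.
- **Ethics and dissemination.** An adverse reaction from the family is discussed as a possible harm and judged highly unlikely on the basis of the feasibility work.

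**The concern.** The smoke-free intervention works through children: they take a promise form home and try to persuade adults not to smoke indoors. If it does harm, the likeliest route is the adults' reaction. The protocol recognises this in two places, but the rule for what counts as an AE is a clinical one of the kind used in treatment trials.

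At stake is the content of the pilot's safety answer. An AE table with few or no events would be carried into the planning of the definitive trial as evidence that the approach is safe for children. Under the stated definition, such a table would be silent on family reactions with no medical consequence, and a reader of the table could not tell that from the count.

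**Working it through.** The plan states no figure on this point, so there is none to reproduce. The check is to run three kinds of event through the stated rules.

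| Event after a child raises smoking at home | In the target of surveillance (AEs procedures, Ethics)? | Meets the AE definition? | AE form required? |
|---|---|---|---|
| Injury or psychological symptom | Yes | Yes | Yes, if reported |
| Punishment, threat or conflict, no clinical consequence | Yes, as an adverse family reaction | No, not a clinical event | No, the form is tied to an AE |
| New cough or runny nose, unrelated | No | Yes, a symptom that has appeared | Unclear if the only record is the diary |

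**Row 1.** Definition and surveillance agree. The section on evaluating AEs then grades causality on four levels, from unrelated to definite, so these events can be separated from background illness.

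**Row 2.** This is the gap. The event is what teachers are likely to notice and what children and parents are invited to mention. The step from a mention to a counted event nevertheless passes through the word AE, and the definition restricts that word to clinical events. The undefined term for connected adversities has no recording route of its own. Followed literally, the number of non-clinical family events counted as AEs is zero, however many occur.

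**Size.** About half of the planned 360 children are in the intervention arm: 6 schools × 30 children = 180. The documents give no rate of non-clinical family reactions. Purely as an assumption, rates of 1% to 5% would mean 180 × 0.01 = 1.8 to 180 × 0.05 = 9 children affected, none of whose events the definition would count. Against an expected minimal number of AEs, even the lower end could change the picture.

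**Comparison of arms.** The occasions on which a child might mention a family reaction informally are not the same in the two arms. Refresher sessions ask children about difficulties met at home, and a member of the research team attends all intervention sessions. Control schools receive the intervention only after the trial. Informal capture therefore cannot stand in for a defined event asked about in the same way in both arms.

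**Row 3.** All 360 children keep the diary to the end of month 2, with 6 upper and 7 lower respiratory items, 13 in all: "Scores will be recorded daily and added up to give daily upper and lower respiratory-tract scores, respectively". A new or worsened symptom fits the words of the AE definition. The recording section neither names the diary as a source of AE reports nor excludes it. This is an ambiguity to settle, and the main point does not depend on it.

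**The case against.** The strongest case on the other side has four parts.

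1. **The working route is wider than the definition.** The AE procedures themselves treat events from child–parent interaction as AEs, invite reports in broader terms, and use a form that needs no diagnosis. The list of examples is illustrative. A sensible research assistant might record a threat or punishment. This stands as a description of what might happen. It also means that the count would depend on staff reading past the definition, and a pilot count should not rest on that.
2. **The pilot question can still be answered.** A reader might infer that the mismatch makes it unanswerable. The documents do not support that. Clinical AEs, including clinical consequences of conflict, can be tabulated by causality, severity and expectedness. The answer would be incomplete, not impossible.
3. **The diary need not swamp the AE count.** A reader might infer that every cold noted in a diary needs an AE form and a same-day call. Only symptoms that appeared or worsened would qualify, the trigger is a report by a child, parent or teacher, and diary sections are collected at follow-up as a secondary outcome. No symptom rate is given either, so no credible number of forms can be stated. How outcome symptoms are handled on AE forms may also be settled in the full protocol, which a journal article condenses.
4. **There is other safety experience.** The pilot should not be called the only safety evidence, because the AE procedures cite previous studies without directly related AEs. That is correct, but it does not repair the definition used here.

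The wording mismatch survives these objections: the definition is stated outright in the article, and it is narrower than the harm the same article asks people to look for.

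**Conclusion.** The concern holds in a limited form. The AE definition does not match the harm that the AE procedures and the ethics section identify, and non-clinical family harm would go uncounted if the text is followed. The answer to the pilot's AE question could therefore miss the harm most specific to this intervention. How many events would be missed is unknown; the 1% to 5% range is an assumption that shows scale only.

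The conclusion rests on reading the definition literally and on the AE form being opened only for events that meet it. It does not touch the estimates of recruitment, attrition, effect size or intracluster correlation. It merits a change because the question concerns children asked to challenge adults, and because the remedy is small. The diary matter is a secondary clarification.

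**What to change.** - **Definition.** In Definitions, Adverse event, widen the wording to: *any untoward clinical or social event (for example punishment, threats, family conflict or distress), whether or not related to the study intervention*. Leaving relatedness out keeps the present approach, in which causality is judged afterwards, and allows the arms to be compared.
- **Reporting.** Tabulate the social events separately from clinical AEs, by arm. The existing causality and severity grades can be applied as they stand.
- **Ascertainment (preferable).** Ask about these events in the same way in both arms at the month-2 contact with all children, and pass any disclosure through the existing AE route. The sections on the primary outcome and the respiratory symptoms diary imply such a contact, whereas Data collection confines follow-up assessments, including month 2, to children with cotinine indicative of exposure at baseline. These sections must be reconciled first.
- **Secondary clarification.** State whether a new or worsened diary symptom is a reported AE for the purpose of the AE form, given the minimal number expected.

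The cost is a change of wording, one extra questionnaire item, and some added AE handling when a child reports a difficulty. Sample size, intervention and primary outcome are unaffected.

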##### Serious adverse event

A SAE is any clinical occurrence that:
Results in death of the participant;Is life-threatening, defined as an event in which the participant is at risk of death during the event. This does not refer to incidents that hypothetically might have led to death if the event worsened;Results in hospitalisation or prolongation of hospital stay;Results in persistent and/or significant disability and/or incapacity;Birth defect or congenital anomaly;Any medical condition that may not be life-threatening, disabling or resulting in hospitalisation but requiring medical or surgical intervention to prevent any of the above outcomes.

Please note that any planned surgery or medical procedure will not be considered as an SAE.

#### Detecting, recording and reporting of AEs and SAEs

In the event of any AE reported by the child, their parents/carers or schoolteachers, the research assistant will complete an AE form, which will include medical diagnosis, if relevant and available. The research assistant will also call the trial manager on the same day providing a verbal report of the event. The trial manager will ensure that the event is classified appropriately after receiving the verbal report. All AEs will be reported to the principal investigator, Bangladesh (RH) within 3 days of detection. AE data will be collated and reported to the trial sponsors and National Bioethics Committee at six monthly intervals. These must also be reported to the Study Operational Committee (SOC) and the Independent Trial Steering Committee (ITSC) at their regular meeting. All AEs that have the potential to develop into SAEs will be followed to resolution or stabilisation and reported as SAEs if they become serious. All SAEs must be reported to the principal investigator within 24 h of detection and should also be reported to the trial sponsors and National Bioethics Committee within three working days. All serious events must also be reported to all study investigators and the chair of the ITSC within 3 days. The chief investigator will have the overall responsibility to ensure that all AEs are reported according to the above protocol.

#### Evaluation of AEs and SAEs

In addition to assessing seriousness, the trial manager will assess all AEs for causality, severity and expectedness.

##### Assessment of causality and relatedness

This will be done in consultation with the principal investigator and the event will be classified as follows.

*Unrelated*: When the event is considered not related to the study intervention.

*Possibly*: When an association of the event with the study treatment cannot be ruled out.

*Probably*: When temporal association and an absence of any other explanation suggest that the event could be related to the study intervention.

*Definitely*: Evidence suggests that the study intervention is the most likely cause of the event.

*Assessment of severity*: The trial manager will make the following assessment based on severity, which should not be confused with seriousness (a statutory definition) differentiating between AEs and SAEs.

*Mild*: Those events that cause minimal discomfort, are easily tolerated and do not interfere with routine life activities.

*Moderate*: Those events that cause moderate discomfort and do interfere with routine life activities.

*Severe*: Those events that cause much discomfort and lead participants to stop their routine life activities.

##### Assessment of expectedness

If the event is judged to be an adverse reaction, serious or otherwise, it must be judged on expectedness based on what is already known about the intervention under study.

#### Follow-up procedures

These events will be followed up until resolution or returning to a stable medical state. We will not expect any events to be relevant to the trial that occur after the completion of follow-up, and therefore no active surveillance will continue beyond trial completion. Nevertheless, any event reported to the trial manager will be recorded and kept in the records along with other trial data.

### Statistical considerations

#### Sample size

This pilot trial will inform sample size considerations for a definitive trial. Therefore, no formal sample size calculations have been undertaken. However, with the number of clusters (and cluster size) we seek to enrol, we should be able to estimate recruitment and attrition rates, effect size and ICC. For our primary outcome, the pilot trial will provide us with a more accurate effect size and SD values. If the effect of intervention is similar to that observed in our feasibility study and implementing smoking restrictions at home imply a reduction in SHS exposure, we should expect 40–50% reduction in children's exposure to SHS. The ICC observed in our feasibility trial was 0.18, but it was estimated for a proximal outcome. Therefore, in this study, we will be able to determine a more accurate estimate of ICC based on a distal outcome. Assuming that at least 360 children (and their parents/carers) agree to participate from each school, we expect at least 120 children with a positive cotinine test as baseline. On the basis of the feasibility trial, we expect no schools to drop out from the trial and the children's attrition rate to be <20%. According to this, we estimate that we will be able to retain at least 96 children by the end of the trial. However, actual attrition rates will be found to make adjustment to the sample size.

#### Statistical analysis

We will conduct a preliminary analysis summarising: participant (individual and cluster) characteristics; attrition rates; likely estimates of effect and ICC for the outcomes. This will also include a comparison between participants with detectable and zero levels of cotinine at baseline. Although determining differences in the outcomes between the two arms is not the purpose of this study, we will summarise outcomes at both cluster and individual levels using an intention-to-treat principle and estimate 95% CIs for any differences. All analyses will be conducted using SAS 9.4 (Institute Inc, Cary, North Carolina, USA).

### Qualitative evaluation

Interview data will be analysed using thematic analysis,^26^ which is a method of ‘identifying, analysing and reporting patterns (themes) within the data’. This is a useful approach for producing qualitative analyses suited to informing programme evaluation and development. The focus of the analysis will be to identify key issues in delivering the SFI that may inform the process of ‘scaling up’ the intervention for the definitive trial. Six phases of thematic analysis will be followed: familiarisation, generating initial codes, searching for themes (prior—informed by study objectives as well as emergent), reviewing themes, defining and naming themes, writing the final report. Negative cases will be actively sought throughout the analysis and emerging ideas and themes modified in response.^27^ NVivo will be used to manage the data.

### Health economics

In the pilot phase of this trial, we will assess the feasibility and acceptability of undertaking a full cost-effectiveness analysis. The first stage will estimate the cost of delivering the intervention. Intervention costs will include the time and resources needed to deliver the SFI intervention. We will also pilot a service use questionnaire to record utilisation of healthcare resources. These include doctor and hospital visits for the treatment of childhood conditions related to the inhalation of passive smoke and also medications dispensed for such illnesses. We will audit and analyse the returned data for completeness and revise questionnaires where appropriate to improve data capture in a full trial.

The purpose of the pilot phase is to inform a cost-effectiveness analysis in a full trial with regard to intervention cost and data collection. In a full trial, we will conduct an incremental cost-effectiveness analysis of the smoke-free homes intervention over and above the control. Total costs include the costs of the intervention (SFI) as outlined above and wider healthcare costs such as doctor and hospital visits for childhood illness related to the inhalation of passive smoke (asthma, wheezing, middle ear infections, respiratory tract infections and meningitis). We will also record and calculate the costs of medications related to these illnesses, which are dispensed. In the full trial analysis, the quantities of resource use (contacts) are multiplied by local unit costs to derive an individual cost profile.

The main outcome for the health economic analysis of the full trial will be changes in quality adjusted life years (QALYs), which will be computed from the EQ-5DY questionnaire^24^ completed by trial participants. In a full trial, we propose a within-trial cost-effectiveness analysis combining the costs of the intervention and wider treatment with QALY gains to derive an incremental cost per QALY. The cost per QALY will inform the value for money afforded by investment in the SFI intervention. We will perform sensitivity analysis to investigate the robustness of the results. We will also explore potential differences in cost-effectiveness between centres within the trial using multilevel modelling techniques.

